## Abstract

**Background:**

Breast cancer (BC) is the most frequent cancer in women with more than 70% of BC patients being treated with hormonal therapy (HT). Among these patients, some report difficulties in remembering what they are supposed to do at the right moment, referring to prospective memory (PM). PM is essential for autonomy and medical adherence of patients, and requires an ecological assessment. Virtual reality, that recreates naturalistic environment, seems to be a promising method to evaluate PM. Several BC patients also report sleep disturbances. Given the role of sleep on memory consolidation, it is imperative to explore the influence of sleep quality on PM in BC patients treated with HT.

The purpose of PROSOM-K study is to assess PM functioning using virtual reality and sleep quality in BC treated or not with HT.

**Methods:**

PROSOM-K is a prospective study including post-menopausal BC patients ≤70 years old treated with radiotherapy (*n* = 25) or with radiotherapy and HT (*n* = 25), and healthy post-menopausal women (*n* = 25) matched for age and education. PM will be assessed using a virtual reality based task. Other cognitive functions and psychosocial factors will be assessed with validated questionnaires and neuropsychological tests. The study is divided in 3 sessions: a session of familiarisation with the virtual environment and the PM task: a day-time session during which participants learn intentions during the morning and recall them in the evening; and a night-time session during which participants learn intentions in the evening and recall them the following morning. Women will be monitored by wrist actigraphy; during the night-time session, objective sleep quality and quantity will be measured by polysomnography.

**Discussion:**

This is a novel study aiming to assess PM using virtual reality, coupled with the evaluation of other cognitive functions. Polysomnographic study of sleep will provide further information about architectural sleep disturbances in BC. Association between sleep architecture parameters and PM mechanism in BC women treated with HT will be described in detail. We expect our results will provide knowledge for patients and clinicians and further help to improve patient care and cognitive therapy.

**Trial registration:**

NCT03420105, registered: January 10, 2018.

**Electronic supplementary material:**

The online version of this article (10.1186/s12885-018-4762-2) contains supplementary material, which is available to authorized users.

## Background

Breast cancer (BC) is the most frequent cancer in women and its incidence is increasing [1]. Among these patients, some of them experience cognitive troubles and especially difficulties remembering what there are supposed to do at the right time or in the right place [2, 3]. These memory lapses concern prospective memory (PM) which refers to our ability to remember to accomplish intended tasks or actions at some predefined point in the future.

PM is divided into two components: prospective and retrospective. The first of these refers to the process of remembering that something has to be done at the appropriate time or event, while the second refers to the memory of what has to be done (action). Prospective component gathers two types of intentions: Time-Based (TB) intention referring to self-initiated retrieval of the action after a period of time has elapsed or at a certain time; and Event-Based (EB) intention when an event occurs and triggers the remembering of the action. Intention retrieval relies on two types of processes used in a Dynamic Multiprocess Framework: monitoring and spontaneous retrieval. Their use depends on various factors, for example, characteristics of intentions and ongoing tasks, and importance of realising the action. Monitoring refers to keeping an intention in mind while searching for the prospective component. Spontaneous associative retrieval process relies on automatic processes that bring a retrospective component into mind when a prospective component appears [4]. PM functioning involves various cognitive functions, such as episodic memory, executive functions, and working memory. Retrospective episodic memory is required for the encoding, retention and recall of the intention [5]. Executive functions are involved in planning the intention, inhibiting the ongoing task, and switching to realise the intended action. Working memory is required to keep the intention in mind between the recall and the realisation of the action, and the binding process induces a link between prospective and retrospective components creating a unitary representation of the intention in working memory [6]. PM is essential for daily living tasks and, in BC patients, PM is even more essential for medical adherence, autonomy, and return to social and professional life.

Despite recurrent complaints of patients about their PM, only a few studies have focused on PM deficits in BC [2, 3, 7–10]. Paquet and colleagues used the Memory for Intention Screening Test (MIST) [11], a common PM task, composed of four EB and four TB intentions to retrieve while completing a word puzzle in the laboratory. A naturalistic task had to be carried out at home 24 h later. The authorsdid not differentiate between EB and TB intentions, but their results revealed decreased performances of patients compared to healthy women [2]. Cheng and colleagues used two laboratory tasks, assessing TB and EB intentions separately. During these tasks, participants had to tap the desk at the target time or event. Results showed a deficit in EB intention retrieval in BC patients [3, 9, 10]. Altogether, results from these studies revealed an impairment of PM in BC patients. However, none distinguished between prospective and retrospective components, which limits the understanding of the impaired processes. In addition to PM, Cheng and colleagues [4–6] assessed general cognitive functioning with Mini Mental State Examination, Verbal Fluency Test, and Digit Span test. Results revealed a significant decrease of cognitive functioning in BC patients compared with healthy women, but the authors did not correlate neuropsychological scores with PM scores. Cognitive functions known to be involved in PM functioning must be evaluated and correlated with PM scores in order to better understand the PM deficits in BC patients.

Furthermore, laboratory PM tasks lack ecological validity. Virtual reality may be suitable to assess PM because it recreates naturalistic situations of daily life while maintaining experimental rigor [6] that is difficult to uphold in naturalistic PM tasks. Other factors associated with BC (depression, stress, anxiety, and fatigue) may affect both cognition and PM [2, 12], and should therefore be taken into account to deepen knowledge about factors implicated in PM deficits in BC patients.

Studies in BC revealed that 39.5% to 69% of patients encounter sleep disturbances, provoked or worsened by cancer and its treatments [13]. The majority of studies used self-report questionnaires and reported sleep disturbances in BC patients. Studies on patients treated for BC using wrist actigraphy to assess motor activity and sleep quality reported a decreased sleep quality. In cancer patients, very few studies have used polysomnography (PSG), the gold standard of objective assessment of sleep. Although results of sleep architecture (particularly percentages of sleep stages) differ between studies using PSG, they showed a deterioration of sleep quality in BC patients. Furthermore, one of the parameters of interest, the Slow Waves Sleep (SWS), involved in memory consolidation, seems to be decreased in cancer patients [14–16].

Sleep is well known to play a part on memory consolidation [17–19]. While consolidation of retrospective memories is well studied, few studies have been published on benefits of sleep in PM although mechanisms might be different. Scullin and McDaniel showed that remembering to execute an intention was improved after a 12 h sleep delay compared to a 12 h wake delay [19]. Diekelmann and colleagues demonstrated that subjects who slept during the early night (mostly composed of SWS), had better scores at intention execution two days later than subjects who had slept during the late night (mostly composed of Rapid Eye Movement sleep) [20]. Sleep, and especially SWS, seems to promote PM consolidation for simple tasks. Results on sleep benefits in more complex and ecological tasks need to be thorough, as well as sleep variables implicated in PM consolidation. In light of SWS involvement in memory consolidation, the link between sleep disturbances and PM deficits in BC patients need to be explored.

Among factors that may have an impact both on memory and sleep disturbances in BC patients, hormonotherapy seems particularly relevant. The majority of studies assessing impact of treatment on BC patients have focused on chemotherapy, while up to 70% of BC patients are treated with hormonal therapy (HT) [21]. Some studies have shown a deleterious impact of HT on patients' cognitive functions, especially memory [22]. Only one study has made an a posteriori analysis about the PM performances at MIST in BC patients treated or not with HT [7]. There were no significant differences between scores of these two groups, probably because components and EB/TB intentions were not differentiated. Furthermore, all patients were also treated with chemotherapy, a treatment known to have an impact on cognitive functioning. Thus, this study does not allow for a conclusive understanding of the impact of HT on PM. Few studies have been published about sleep disturbances in BC treated with HT. Additionally, these studies have mostly used self-report questionnaires about sleep quality and results are inconclusive [23]. Some studies reported insomnia complaints from patients treated with HT [24], while others did not [25].

Further studies are, therefore, needed to confirm the impact of HT on PM and sleep in BC patients. This also warrants to implement studies with ecological tasks taking into account the different components of PM coupled with complementary neuropsychological tests to understand processes impaired. Furthermore, no study has assessed the influence of sleep disturbances on PM in BC patients.

The purpose of PROSOM-K is to evaluate cognitive functions underlying PM impairment in BC patients using an ecological task and virtual reality. Further, we aim to assess sleep disturbances encountered by BC women treated or not with HT and their impact on PM functioning.

## Methods

### Study objectives

The primary objective of the PROSOM-K study is to assess PM performances in BC patients, in order to determine which components (prospective or retrospective), and types of intentions (EB or TB) are the most impaired in BC patients, and specify which cognitive processes (episodic memory, working memory, or executive functions) are particularly involved in PM decline in BC patients.

The secondary objectives are to:clarify the influence of sleep disturbances in BC on PM deficits, using various sleep quality assessments (polysomnography, actigraphy and self-report questionnaires), and by comparing PM scores in two different conditions, depending on the type of delay between encoding and retrieval of intentions: day-time and night-timeassess the influence of HT on PM functioning by comparing PM scores between BC patients treated with HT and BC patients not treated with HT.

### Participants

The PROSOM-K study will include 25 BC patients treated with radiotherapy alone, 25 BC patients treated with radiotherapy and HT, and 25 healthy women. Patients will be recruited in Centre François Baclesse, a regional cancer centre in Caen (Normandy, France). PROSOM-K protocol will be proposed to eligible patients during a follow-up medical care with their oncologist. Healthy volunteer women, matched for age and years of education with BC patients, will be recruited from our laboratory. Once verified the eligibility criteria (see Table 1) by a physician, each participant will provide her written informed consent to be enrolled in PROSOM-K protocol.

**Table 1 Tab1:** PROSOM-K inclusion and non-inclusion criteria

	Breast cancer patients	Healthy women
Inclusion criteria	1 year post-menopausal	
	Under 70 years of age	
	At least on level 3 (end of primary schools) of the Barbizet scale	
	French native speakers	
	Treated with surgery or radiotherapy for a non-metastatic breast cancer	Normal cognitive function with the Montreal Cognitive Assessment (MOCA) score ≥ 26
	Radiotherapy completed about 6 months prior to the study	–
Non-inclusion criteria	Neurological sequelae	
	Personality disorders and progressive psychiatric disorder	
	Drug use and/or heavy drinking	
	Treated with chemotherapy	History of cancer, excepting basal-cell carcinoma and carcinoma in situ of the uterine cervix
	Patient with a paraneoplastic syndrome	–
	Patient unable to perform cognitive tests	–
	Central nervous system primitive tumour or cerebral metastases	–
	Primitive cancer different from Breast cancer	–
	Metastatic cancer	–
	Cognitive disorders pre-existing to cancer diagnosis	–

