#### Complementary cognitive assessment

During each session, cognition will be assessed using neuropsychological tests (see Table 3). Global cognitive functioning will be assessed with the Montreal Cognitive Assessment (MoCA) [26], and the crystallised intelligence with the Mill Hill part B [27]. Retrospective episodic memory will be assessed with the French adaptation of Grober and Buschke’s procedure [28]. Working memory will be assessed using the Digit Span forward and backward test (Wechsler Adult Intelligence Scale-III [29]), and the binding process will be assessed using a multimodal integration task [30]. During the multimodal integration task, participants have to mentally associate four coloured letters and the location of the cross of the same colour in a grid. Then a grid appears with a black letter, and participants have to indicate if the letter-location corresponds to the letter-location of the mental association. Executive functioning, especially planning, inhibition, shifting, and updating, which are known to be involved in PM functioning, will be assessed respectively with: the Zoo map test [31], the Stroop [32], the Trail Making Test [33], and the N-back task [34].

**Table 3 Tab3:** Neuropsychological tests battery and questionnaires included in the PROSOM-K study, including outcomes measures

Domain assessed	Assessments	Outcome measures	Range
Neuropsychological tests			
Global functioning	MOCA [26]	Total number of correct responses	0–30
	Mill Hill [27]	Total number of correct responses	0–34
Episodic memory	RL/RI-16 [28]	Immediate free recall score	0–48
		Immediate total recall score	0–48
		Delayed free recall score	0–16
		Delayed total recall score	0–16
Working memory	Digit span forward and backward [29]	Total number of correct trials forward	0–16
		Total number of correct trials backward	0–16
	Multimodal integration task [30]	Total number of correct responses	0–20
Executive functions	Zoo map test [31]	Profile score	0–4
	Stroop [32]	interference–colour (time)	≥0 s
	TMT [33]	TMT B–TMT A (time)	≥0 s
		Perseverative errors TMT B (number)	≥0
	N-back [34]	Total number of correct responses	0–48
Questionnaires			
Cognitive self-assessment	Fact-Cog [35]	PCI/PCA/QOL/Oth	0–72/0–28/0–16/0–16
	PRMQ [36]	Prospective score	8–40
		Retrospective score	8–40
Anxiety	STAI [39]	State score	20–80
		Trait score	20–80
Mood	BfS/BfS’ [45]	Total score / Total score	0–56 / 0–56
Depression	BDI [40]	Total score	0–39
Self-esteem	QSR [38]	Valence score	0–100%

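### Healthy women must reach MoCA 26 to enter but patients face no score, which tilts patient-versus-control contrasts towards apparent patient impairment by an amount the protocol does not fix

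*Protocol article*

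**What the plan says.** Table 1 (Methods, Participants) has one column for patients and one for healthy women. The healthy-women column lists as an inclusion criterion "Normal cognitive function with the Montreal Cognitive Assessment (MOCA) score ≥ 26". The patient cell in the same row is about treatment: "Treated with surgery or radiotherapy for a non-metastatic breast cancer".

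Two patient criteria touch on cognition, both as non-inclusion criteria and both blank for healthy women: "Cognitive disorders pre-existing to cancer diagnosis" and "Patient unable to perform cognitive tests". Neither names a test score.

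Controls are otherwise aligned with patients on two variables: "Healthy volunteer women, matched for age and years of education with BC patients, will be recruited from our laboratory".

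MoCA is also a study measure, listed in Table 3 with range 0–30. The section on complementary cognitive assessment says "Global cognitive functioning will be assessed with the Montreal Cognitive Assessment (MoCA").

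The Background states that "PM functioning involves various cognitive functions, such as episodic memory, executive functions, and working memory", and under Study objectives "The primary objective of the PROSOM-K study is to assess PM performances in BC patients". The Discussion uses the healthy group as the reference for any effect of breast cancer or HT. The article gives no reason for the control-only threshold, and its limitations paragraph covers only discomfort in virtual reality.

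**The concern.** A healthy comparison group should show how women like the patients would perform without cancer. Some women of this age score below 26 on MoCA without any known disorder. Under Table 1 such a woman enters if she is a patient and is refused if she is a volunteer.

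The volunteers are thus cut from below on a variable related to the outcome, and the patients are not. With any positive MoCA-PM correlation, the control PM mean is raised by the entry rule alone. Part of an observed gap would then reflect who was admitted, not cancer or its treatment, and the error runs in the direction of the study's hypothesis. For MoCA itself the cut is direct: controls can only score 26 to 30 at entry. Matching on age and education does not undo selection on cognition within age and education strata.

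**Working it through.** **No figure of the plan is in dispute here.** The protocol gives no estimate of this effect to reproduce, so the check asks how large the shift could be.

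**Inputs**
- From the document: threshold of 26 for controls only; 25 women per group; α = 0.05 (taken as two-sided; the article does not say).
- Assumed, because the document gives neither: q, the share of otherwise eligible volunteers scoring below 26 (5%, 10%, 20%, 30%); r, the MoCA-PM correlation given age and education (0.3 to 0.5).
- Simplification: patients are treated as not screened on cognition at all.

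**Model.** MoCA and PM are bivariate normal, with no true difference between patients and healthy women. Let a be the q-quantile of the standard normal and φ its density.

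1. Rise in control MoCA mean, in SD: λ = φ(a)/(1 − q).
2. Rise in control PM mean, in SD: d = r·λ.
3. Standard error of the difference at 25 versus 25, unit SDs: √(1/25 + 1/25) = 0.283.
4. Two-sided rejection rate with no true effect: Φ(d/0.283 − 1.96) + Φ(−d/0.283 − 1.96).

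**Example, q = 20%, r = 0.3.** a = −0.842, φ(a) = 0.280, λ = 0.280/0.80 = 0.350. Then d = 0.3 × 0.350 = 0.105 and d/0.283 = 0.371. The rejection rate is Φ(−1.589) + Φ(−2.331) = 0.056 + 0.010 = 0.066.

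| q removed | λ (MoCA shift, SD) | d (PM shift, SD), r = 0.3 to 0.5 | False-positive rate, 25 vs 25 |
|---|---|---|---|
| 5% | 0.109 | 0.03–0.05 | 5.2–5.4% |
| 10% | 0.195 | 0.06–0.10 | 5.5–6.4% |
| 20% | 0.350 | 0.10–0.17 | 6.6–9.5% |
| 30% | 0.497 | 0.15–0.25 | 8.2–14.2% |

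Truncation also narrows the control PM distribution slightly (SD 0.93 at q = 30%, r = 0.5). Allowing for that moves the last figure from 14.2% to 14.8%, which changes nothing of substance.

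If the same rule applied to all groups, or to none, this selection shift would be 0 and the rate 5%.

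**Which contrasts are reached.** Only those between patients and healthy women. HT versus no HT compares two patient groups under the same criteria. Day versus night is within person. Associations of PM with sleep or cognition within patients do not involve the controls.

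**The case against.** - **Low MoCA in patients may be the effect under study, so they cannot be held to 26.** This is right, and it rules out a patient cut-off as the main remedy. It does not justify a cut-off for controls.
- **A cognitively normal reference group is a recognised design.** It is, but the contrast then answers a different question, namely patients against screened-normal women, and should be described so.
- **Patients are screened too.** The two patient exclusions remove some low scorers and are not netted off in the table above, so its figures are on the high side. They narrow the imbalance without closing it, because neither sets a level of current performance.
- **The size is assumed.** This stands. If few volunteers score below 26, the effect is negligible.
- **The primary objective is partly about profile.** Asking which component or intention type is most impaired is less sensitive to a roughly uniform rise in controls than the overall gap is. This stands too.

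Two stronger readings are tempting. A reader might infer that the threshold contradicts the sample-size assumption of 10% cognitive decline among healthy controls. The article does not define decline or tie it to MoCA, and a woman at or above 26 may still do poorly on a PM or executive test, so no conflict is shown. A reader might also infer that the primary comparison is materially inflated. The document supports the direction, but not any particular size.

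**Conclusion.** The unequal entry rule is stated plainly in Table 1, and the direction of its bias follows from the protocol's own account of PM, given a positive MoCA-PM correlation. The point is confined to patient-versus-control contrasts in PM, MoCA and the neuropsychological battery.

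The magnitude is open. It ranges from near nil when 5 to 10% of volunteers are refused to a modest but real shift when 20 to 30% are refused. These figures rest on the assumed q and r, on normality, and on ignoring the patient history exclusions, which would reduce them. The point merits correction because the bias favours the hypothesis, the article does not disclose it, and the remedy is cheap.

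**What to change.** **If recruitment of controls can still change:** replace the control-only MoCA threshold in Table 1 with the same history-based exclusion in all groups (no known cognitive disorder), and keep MoCA as a measured variable. This is a one-line change. Its cost is that an occasional control with unrecognised impairment may enter, slightly raising the variance and lowering the control mean.

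**If controls are already enrolled under the rule:**
- Report how many volunteers were refused on MoCA. This supplies the q that the document lacks.
- Add a sensitivity analysis restricting patients to MoCA of at least 26. The data are already collected. Present it as a conservative bound, since it may remove real impairment.
- Describe the main contrast as 'versus cognitively screened controls'.

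Adjusting for MoCA as a covariate is not a clear substitute, because MoCA may lie on the path from cancer or treatment to PM.

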### Virtual environment

The three-dimensional immersive environment has been designed and developed by the Interdisciplinary Centre for Virtual Reality (CIREVE) in Caen (Normandy, France). The environment is a virtual reproduction of the Memorial Museum in Caen. The immersive room (CAVE, Cave Automatic Virtual Environment) is composed of four wide screens for 3D stereoscopic projection: two laterals (9 × 3 m), one facial (4.80 × 3 m), and one on the floor (9 × 4.80 m). Participants will wear stereoscopic glasses with position sensors able to compute perspective in real time. Participants will be placed at the centre of the floor screen [see Additional file 1] and will move using a joystick that also allow them to project the fictional time and a map of the Memorial onto the screen.

